## Abstract

**Introduction:**

Burn-induced changes in the phenotype and function of neutrophils, cells which provide front-line protection against rapidly dividing bacterial infections, are emerging as potential biomarkers for the early prediction of sepsis. In a longitudinal study of adult burns patients, we recently demonstrated that a combined measurement of neutrophil phagocytic capacity, immature granulocyte (IG) count and plasma cell-free DNA (cfDNA) levels on the day of injury gave good discriminatory power for the prediction of later sepsis development. However, limited by a small sample size, single-centre design and focus on adult burns patients, these biomarkers require prospective validation in a larger patient cohort. The Scientific Investigation of the Biological Pathways Following Thermal Injury-2 study aims to prospectively validate neutrophil phagocytic activity, IG count and plasma cfDNA levels as early prognostic biomarkers of sepsis in thermally injured adult and paediatric patients.

**Methods and analysis:**

This multicentre, longitudinal, observational cohort study will enrol 245 paediatric and adult patients with moderate to severe burns within 24 hours of injury. Blood samples will be obtained at 19 postinjury time points (days 1–14, day 28, months 3, 6, 12 and 24) and analysed for neutrophil phagocytic activity, IG count and cfDNA levels. Patients will be screened daily for sepsis using the 2007 American Burn Association diagnostic criteria for sepsis. In addition, daily multiple organ dysfunction syndrome and Sequential Organ Failure Assessment Scores will be recorded relationships between neutrophil phagocytic activity, IG count and plasma cfDNA levels on day 1 of injury and the development of sepsis will be examined using logistic regression models.

**Ethics and dissemination:**

This study received ethics approval from the West Midlands, Coventry and Warwickshire Research Ethics Committee (REC reference:16/WM/0217). Findings will be presented at national and international conferences, and submitted for publication in peer-reviewed journals.

**Trial registration number:**

NCT04693442.

Strengths and limitations of this studyThis study’s main strength is its immediate (days 1–28) and long-term (months 3–24) analysis of the immune and inflammatory response to severe thermal injury in both paediatric and adult patients.Analysis of immediate and long-term postinjury blood samples will allow for kinetic profiling of the immune and inflammatory response to severe thermal injury.Centred on the analysis of innate immune function, this study will offer little insight into the immediate and long-term changes in the adaptive immune system following thermal injury.

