## Introduction

Built on such clinical practices as early burn excision and wound closure, goal-directed fluid resuscitation and early enteral feeding, modern day burn care has markedly improved the initial outcomes of thermally injured patients, who now survive injuries that were fatal less than 30 years ago.^1^ However, with such unprecedented survival rates, new challenges in the management of hospitalised burns patients have emerged. With an incidence rate of between 23%–63% in paediatric burns patients^2–4^ and 8%–42.5% in adult burns patients,^5^ sepsis is a common complication following thermal injury. Defined as ‘life-threatening organ dysfunction caused by a dysregulated host response to infection’,^6^ postburn sepsis is associated with significantly increased lengths of intensive care unit and hospital stay, and is the leading cause of mortality among hospitalised burns patients, accounting for between 28%–65% of deaths in adult patients^5^ and 47% of deaths in paediatric patients.^7^ Understanding the mechanisms underlying the development and progression of sepsis is therefore critical if we are to improve patient outcomes postburn.

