### Sample size

The sample size for this study is based on data collected from adult patients recruited into the SIFTI-1 study.^18^ Of the 57 adult burns patients who survived for at least 7 days following study enrolment, 35 developed sepsis, equating to a prevalence of 61%. Of these, 33 patients, with a TBSA burn ≥15%, had measurements of neutrophil phagocytic capacity, plasma cfDNA levels and IG count recorded on day 1 of injury. These data provided good discriminatory power to identify septic patients, with logistic regression modelling providing an area under the ROC of 0.935. Adjusted for shrinkage following internal bootstrap model validation to account for potential overfitting, this model exhibited a specificity of 0.75 and a sensitivity of 1.00. Based on this information, we computed the sample sizes required to estimate a 95% CI for sensitivity (with a maximum width of 10%) and for specificity (with a maximum width of 20%) for prevalence rates of sepsis ranging from 50% to 70%. Assuming a prevalence of sepsis of at least 60% and that the ‘true’ sensitivity is at least 90% and the ‘true’ specificity is at least 70%, these analyses revealed a total of 220 patients would allow us to reliably rule out a sensitivity less than 84% and a specificity of less than 59%. Assuming that the 10% drop-out rate we recorded for patients over the first 7 days of the SIFTI-1 study holds true for this follow-on study, then a total sample size of 245 burns patients, which includes both adult and paediatric age groups, is required for the SIFTI-2 study.

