#### Blood sampling

The schedule for blood sampling of adult and paediatric burns patients and the blood volumes that will be obtained are outlined in figure 2. For children, the volume of blood that will be acquired on days 1, 3, 5, 7, 10, 12, 14 and 28 as well as months 3, 6, 12 and 24 postburn will be dependent on their weight (table 2). For adult burns patients treated with low molecular weight heparin, blood samples on study days 5, 10 and 14 will be obtained 3 hours post-treatment. Blood samples will be taken following local standard operating procedures either from an arterial or central venous line or via venepuncture. The source of the blood samples will be dependent on the type of intravenous access the patient has. Posthospital discharge, research follow-up visits will take place during the patient’s clinical follow-up appointments where possible. For HCs, 9 and 18 mL blood samples will be acquired from paediatric and adult volunteers, respectively, by venepuncture.

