We will determine in how many participants the measurements of neutrophil phagocytic capacity, plasma cfDNA levels and IG count on day 1 of injury predicted a diagnosis of sepsis. This proportion will be reported along with 95% CIs calculated by binomial exact methods. The accuracy of this day 1 biomarker model will be determined through standard estimates of sensitivity, specificity, predictive values and likelihood ratios, with 95% CIs. We will investigate the value added by this day 1 biomarker test when compared with information obtained from other potentially informative sets of biomarkers (eg, revised Baux score). These combinations of tests will be assessed using logistic regression models. Using multivariable logistic regression analysis, we will also generate predictive probabilities for various combinations of these candidate biomarkers. This logistic modelling will aim to derive a prognostic regression function (ie, probability of sepsis) using the day 1 values of each candidate biomarker and other demographic or burn-related variables. Models of varying complexity may be compared through ROC analyses. Longitudinal data collection will enable us to examine how the performance of these models change over time. Limitations associated with the logistic regression approach lie mainly in its generalisability to other data sets. Thus, techniques such as bootstrapping to enhance generalisability will be applied for model validation. In sensitivity analyses, missing data will be estimated by multiple imputation and maximum-likelihood methods, as appropriate, in order to explore the potential bias and reduced statistical power associated with listwise deletion.

Serial sampling will allow for repeated measures analyses of our candidate biomarkers, enabling us to model their kinetics over time and examine how this differs between septic and non-septic patients. For the analysis of longitudinal data, continuous outcomes will be analysed using linear regression to compare the septic and non-septic groups, with mean differences and 95% CIs reported. For other outcomes, analysis of daily measurements will be performed using generalised linear mixed models to account for the hierarchical structure of the data. Summaries of model output will be provided with model effects presented both as estimates with associated 95% CIs and also, where appropriate, as plots to visualise the time course of fitted outcomes.

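### The methods named for the continuous biomarkers over time contrast whoever is alive and sampled at each time point, so loss of the sickest septic patients may be mistaken for immune recovery

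*Protocol article*

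**What the plan says.** The strengths list claims that "Analysis of immediate and long-term postinjury blood samples will allow for kinetic profiling of the immune and inflammatory response to severe thermal injury". The Data collection and patient outcomes section sets two longitudinal questions: how long immune changes last compared with healthy controls, and how septic and non-septic patients differ over time.

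The Data analysis section then names the methods.

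- Laboratory data from controls and patients at the different time points are compared by one-way ANOVA with Dunnett's test, or by Kruskal-Wallis with Dunn's test.
- Serial sampling is said to permit repeated measures analyses of the candidate biomarkers.
- The next sentence, however, says that "continuous outcomes will be analysed using linear regression to compare the septic and non-septic groups, with mean differences and 95% CIs reported". Generalised linear mixed models follow, but for the other outcomes.
- Missing data appear once, at the end of the paragraph on the day 1 prediction models and for sensitivity analyses only: "missing data will be estimated by multiple imputation and maximum-likelihood methods, as appropriate".

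No part of the Data analysis section mentions death. The Introduction says that sepsis "is the leading cause of mortality among hospitalised burns patients". Table 1 lists date of death in the column for days 2–14.

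**The concern.** Neutrophil phagocytic capacity, immature granulocyte count and plasma cfDNA are continuous, so as written they fall under ANOVA or Kruskal-Wallis and linear regression, not under the mixed models. One-way ANOVA and Kruskal-Wallis treat each time point as a separate group of people. Ordinary linear regression does not link a patient's late value to that patient's early value.

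The set of people sampled changes between day 1 and month 24, and death is one reason. Death is tied to the variable that defines the groups. If it is also tied to the marker, the septic mean moves towards the non-septic and control means as the worst-affected patients leave, even when no patient changes. The question of how long immune changes persist would then receive too short an answer, and the difference between septic and non-septic patients would seem to fade.

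**Working it through.** **1. The plan's own figures, to show what is not touched.** The Sample size section inflates 220 for "the 10% drop-out rate we recorded for patients over the first 7 days of the SIFTI-1 study": 220 / (1 − 0.10) = 244.4, rounded up to 245, as stated. At 60% prevalence, 220 patients give 132 septic and 88 non-septic. The exact two-sided 95% lower limits are 83.6% for a sensitivity of 90% (n = 132) and 59.3% for a specificity of 70% (n = 88), matching the stated 84% and 59%. These figures concern day 1 prediction and do not depend on the longitudinal method.

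**2. Inputs the documents do not give.** They give no mortality by sepsis status and no association between any marker and death. The Introduction gives only sepsis's share of burn deaths. Everything below rests on assumed values, and every scenario has a marker that never changes within a patient.

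**3. Gap among survivors, logistic death model.** Take a marker y with SD 1, mean 0.5 in septic and 0 in non-septic patients, where higher is worse. Within group g, P(death | y) = 1 / (1 + exp(−(a_g + ln(OR)·y))), with a_g set so that mortality in the group equals the assumed value. The gap is the mean of y in septic survivors minus the mean in non-septic survivors.

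| Mortality septic / non-septic | OR per SD | Septic survivors | Non-septic survivors | Gap (true 0.50) | Apparent shrinkage |
|---|---|---|---|---|---|
| 15% / 3% | 2 | 0.40 | −0.02 | 0.42 | 0.08/0.50 = 16% |
| 25% / 5% | 2 | 0.34 | −0.03 | 0.37 | 0.13/0.50 = 26% |
| 25% / 5% | 3 | 0.27 | −0.05 | 0.32 | 0.18/0.50 = 36% |
| 35% / 5% | 3 | 0.19 | −0.05 | 0.24 | 0.26/0.50 = 52% |
| any | 1 | 0.50 | 0.00 | 0.50 | 0% |

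With 60% septic, the mean over all patients, which is what is set against controls, falls by 0.08 to 0.23 SD across the first four rows.

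**4. A second model.** Let ρ be the correlation between a static normal marker and the liability to die, and m the septic mortality. The septic survivor mean shifts by ρ·φ(z_m)/(1 − m) SD, with z_m = Φ⁻¹(m). For m = 30% and ρ = 0.5 this is 0.5 × 0.348 / 0.70 = 0.25 SD.

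| m | ρ = 0 | ρ = 0.3 | ρ = 0.5 | ρ = 0.7 |
|---|---|---|---|---|
| 10% | 0 | 0.06 | 0.10 | 0.14 |
| 20% | 0 | 0.11 | 0.18 | 0.25 |
| 30% | 0 | 0.15 | 0.25 | 0.35 |
| 40% | 0 | 0.19 | 0.32 | 0.45 |

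**5. Does the choice of method matter?** Sixty data sets were simulated, each with 147 septic and 98 non-septic patients (60% and 40% of 245). Assumed mortality was 30% and 5% and the marker–death correlation 0.6, with no true change over time; here a lower marker is worse. Among those sampled, the mean gap moved from −0.79 on day 1 to −0.61 at month 6. Regression on independent observations reports that movement as a septic-by-time effect: −0.61 − (−0.79) = +0.18. A random-intercept mixed model on the same data gave +0.01.

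**The case against.** The best defence is that the section announces repeated measures analyses of these biomarkers, and step 5 shows that such a model removes nearly all of the artefact. That stands as far as it goes, and it is why the remedy is cheap. But the next sentence assigns continuous outcomes to linear regression and keeps mixed models for the rest, so the announcement and the named method do not agree for the three markers in question. This is a method stated in the text, not a detail left to an analysis plan that is not shown.

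Three stronger readings are tempting, and the documents do not support them.

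- *The plan would impute marker values after death.* The imputation sentence belongs to the day 1 prediction paragraph and is limited to sensitivity analyses. Nothing extends it to the kinetic profiles. It is a caution for the future only.
- *Late samples depend on clinic attendance.* Research visits are to coincide with "clinical follow-up appointments where possible". That concerns joint scheduling and is no evidence of marker-related loss.
- *The strengths statement is itself an error.* It names no analysis. The problem lies in the Data analysis section.

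It is also fair that the long-term aim concerns survivors: the article links the serial data to complications that survivors report. Values among those alive are a legitimate late target. The difficulty arises when they are set against day 1 values from everyone and the difference is called a time course. A mixed model has a limit of its own, since its fitted means describe a course in which those who died are still measured.

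**Conclusion.** The point holds as a risk, not as a demonstrated bias. The comparisons named for the continuous biomarkers do not separate change within patients from change in who is sampled, and the grouping variable is tied to death. A reader might infer that results *will* show false recovery. The documents do not support that, because neither mortality by sepsis status nor the marker–death association is given.

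The septic versus non-septic gap is not distorted at all if marker and death are unrelated. Under 15–35% septic and 3–5% non-septic mortality, with odds of death multiplied by 2–3 per SD, a constant gap of 0.50 SD would appear as 0.24–0.42 SD. The primary day 1 analysis and the sample size of 245 do not change. The matter should be corrected before the longitudinal results are analysed, but it does not threaten the main objective.

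**What to change.** 1. For phagocytic capacity, immature granulocyte count and cfDNA over time, name a within-patient repeated-measures (mixed) model fitted to measured samples, in place of one-way ANOVA or Kruskal-Wallis and ordinary linear regression.
2. If imputation is extended to longitudinal data, state that nothing is imputed after death.
3. Word month 3–24 results as applying *among survivors*.
4. Report numbers alive and numbers sampled by sepsis status at each time point, and show day 1–14 values separately for patients with and without late samples.
5. Use paired early-versus-late contrasts only as a supporting check, since they discard data that the mixed model uses.

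The cost is revised analysis wording, a table of counts and one figure, with no new patients or samples. Table 1 lists date of death only under days 2–14, so the team should confirm that later deaths are captured for item 4. The downside is a little more analysis and a narrower late claim.

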## Introduction

Built on such clinical practices as early burn excision and wound closure, goal-directed fluid resuscitation and early enteral feeding, modern day burn care has markedly improved the initial outcomes of thermally injured patients, who now survive injuries that were fatal less than 30 years ago.^1^ However, with such unprecedented survival rates, new challenges in the management of hospitalised burns patients have emerged. With an incidence rate of between 23%–63% in paediatric burns patients^2–4^ and 8%–42.5% in adult burns patients,^5^ sepsis is a common complication following thermal injury. Defined as ‘life-threatening organ dysfunction caused by a dysregulated host response to infection’,^6^ postburn sepsis is associated with significantly increased lengths of intensive care unit and hospital stay, and is the leading cause of mortality among hospitalised burns patients, accounting for between 28%–65% of deaths in adult patients^5^ and 47% of deaths in paediatric patients.^7^ Understanding the mechanisms underlying the development and progression of sepsis is therefore critical if we are to improve patient outcomes postburn.

Characterised by elevated circulating concentrations of proinflammatory cytokines and immune activation, severe thermal injury results in a systemic inflammatory response syndrome (SIRS).^8^ This immediate and persistent inflammatory and hypermetabolic state triggers a physiological response in burns patients that mirrors that observed in patients with sepsis. Indeed, fever, tachycardia and tachypnoea, which were included by the American Burn Association (ABA) in their latest criteria for diagnosing sepsis among hospitalised burns patients,^9^ are examples of some of the clinical manifestations used to identify patients with SIRS.^10^ Thus, in response to a sterile insult, burns patients exhibit many of the classic diagnostic biomarkers of sepsis, thereby making the diagnosis of this secondary complication extremely difficult. Faced with this clinical challenge, a number of studies have searched for prognostic and diagnostic biomarkers of postburn sepsis. To date, a number of potential candidates, which include procalcitonin, tumour necrosis factor-alpha, interleukin (IL)-6 and IL-8, have been identified.^11^ However, as with clinical parameters, these markers of inflammation are elevated during the initial SIRS response triggered by sterile burn injury,^8^ which may explain why statistical models built on these biomarkers to predict postburn sepsis in children and adults exhibit poor sensitivity and specificity.^12 13^ Given that for every hour delay in the treatment of sepsis, the risk of death increases by 4%,^14^ there is an urgent need to identify novel biomarkers that can be used to accurately predict sepsis in thermally injured patients.

Providing immediate front-line protection against rapidly dividing bacterial and fungal infections, neutrophils are critical effector cells of the innate immune system. Severe thermal injury has been shown to lead to impairments in a range of neutrophil functions such as chemotaxis,^15–17^ phagocytosis,^17–19^ generation of reactive oxygen species^18 19^ and the formation of neutrophil extracellular traps, which contribute to circulating cell-free DNA (cfDNA).^18^ Given their critical role in the elimination of bacterial infections, this postburn reduction in neutrophil function has been proposed to underlie the increased susceptibility of thermally injured patients to nosocomial infection and sepsis. Interestingly, results from a number of recent longitudinal studies suggest that an early assessment of the phenotype and/or function of the circulating neutrophil pool can be used to predict, diagnose and/or monitor postburn sepsis.^15 18 20^ In a cohort of 13 patients with major burns, Jones *et al* demonstrated that neutrophils isolated from patients during a septic episode displayed a spontaneous migratory phenotype that was significantly different to that recorded for neutrophils isolated from burns patients with or without SIRS.^15^ Importantly, demonstrating both its prognostic utility and monitoring potential, this phenotype was also observed in patients prior to sepsis diagnosis and was corrected following effective antibiotic treatment.^15^ Extending these observations, we recently demonstrated, in a cohort of adult burns patients, that a combined measure of neutrophil phagocytic capacity, immature granulocyte (IG) count and plasma cfDNA levels exhibited strong discriminatory power (area under receiver operating characteristic, AUROC 0.935) on day 1 of injury for distinguishing between patients who did or did not develop sepsis.^18^ Moreover, we found that a statistical model that combined the variables of neutrophil phagocytosis and IG count with a clinical scoring metric (revised Baux score) provided discriminatory power (AUROC 0.986) that was greater than any variable alone.^18^ Although highlighting the potential utility of combined clinical and immune biomarker data for the early prediction of sepsis, our original study was designed to be exploratory and hypothesis generating in nature rather than confirmatory, and as such lacked a formal power calculation. Moreover, the study was limited by its small sample size, single-centre design and the inclusion of data only from adult burns patients. Thus, a much larger study that prospectively validates this novel suite of biomarkers in both adult and paediatric burns patients is required.

### Primary objective

To validate neutrophil phagocytic activity, IG count and plasma cfDNA levels as early biomarkers of sepsis in adult and paediatric thermally injured patients.

## Methods and analysis

### Study design

The Scientific Investigation of the Biological Pathways Following Thermal Injury-2 (SIFTI-2) study is a multicentre, prospective, longitudinal observational cohort study of children and adult patients with moderate and severe burn injury: ≥15% of the total body surface area (TBSA) in adults and≥20% TBSA in children.

